#### Adverse events and monitoring safety

All unexpected adverse events related to KRG intake will be reported to the investigator by subjects and write on the individual case report form by the investigator. Safety will be assessed by the reporting of clinical laboratory tests, vital sign measurements, and adverse events. Clinical laboratory tests, including AST/ALT, BUN/creatinine, red blood cell (RBC) count, white blood cell (WBC) count, hemoglobin, hematocrit, number of platelets, and number of differentiated cells will be determined at weeks 0 (baseline) and 12 (end of the trial). Vital signs of each subject will be checked with monitoring of adverse events (nausea/vomiting, fatigue, allergic reaction, and any adverse events related to KRG extract intake) after each visit.

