### Randomization

After enrollment, subjects will be randomly assigned to one of the two groups, either the KRG group or placebo group. The allocation ratio will be 1:1 in blocks of 2. Randomization will be performed at a site remote from trial location. Random numbers will be generated by a computerized random-number generator through the block-randomization method of a software program (Excel, Microsoft Office 2007) for sequence generation. At the time of randomization subjects will draw an envelope. Each envelope contains a number that is concealed to the treatment allocation. Randomization sequence and allocation will be concealed to all study subjects, research staff, investigators and pharmacists until completion of the study. The allocation list will be protected by password access files and held by a non-investigator independent. In the event of an emergency medical situation the individual's randomization code and group allocation can be identify.

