### Outcome measures

Subjects will be asked open-ended questions about frequency, severity, and duration of ILI symptoms during telephone follow-ups on days 1, 28, 57, and 85 of treatment and days 35 post-treatment. Subjects will be also asked to report the study nurse immediately (within 24 hours), at the onset of ILI symptoms. Any unfavorable or unintended sign or symptom will be documented.

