#### Secondary outcomes

Secondary outcomes will be variety ILI symptoms (including fever, rhinorrhea, nasal congestion, sore throat, cough, sputum, dyspnea, diarrhea, mawkishness, vomiting, headache, and myalgia), severity of ILI symptoms, and duration of ILI symptoms. These outcomes will be checked weekly via telephone. The schedule of assessments is presented in Table 1.

**Table 1 T1:** A brief study schedule at every visit.

	*Screening* *Visit 1*	*Baseline* *Visit 2*	*Visit 3*	*Visit 4*	*Visit 5*	*Follow up* *(Visit 6)*
	
	*D-21* *~D-1*	*Week 0* *D0*	*Week 4* *D28*	*Week 8* *D56*	*Week 12* *D84*	*Week 17* *D119*
***Informed consent form ***	◯					

***Demographic information taking^1 ^***	◯					

***Medical history taking ***	◯	◯	◯	◯	◯	

***Inclusion/exclusion criteria check ***	◯	◯				

***Physician examination^2 ^***	◯				◯	

***Vital sign measurement ***	◯	◯	◯	◯	◯	

***Concomitant drugs check ***	◯	◯	◯	◯	◯	

***Electrocardiogram(ECG) ***	◯				◯	

***Questionnaires for symptoms related to ILI^3^***	◯	◯	◯	◯	◯	◯

***Laboratory test^4 ^***	◯				◯	

***Study product distribution ***		◯	◯	◯		

***Compliance checking ***			◯	◯	◯	

***Adverse event monitoring ***			◯	◯	◯	◯

^◯ ^*: Item need to be performed during the visit*

^1 ^Sex, date of birth, age, contact address and phone number

^2 ^Include present illness, past history taking

^3 ^Frequency of ILI symptom onset, severity of ILI symptoms, and duration of ILI symptoms

^4 ^Blood test (WBC, RBC, hemoglobin, hematocrit, platelets count, AST, ALT, ALP, gamma-GTP, albumin, BUN, creatinine, glucose, total bilirubin, total protein), urine test (specific gravity, pH, protein, ketone, glucose, bilirubin, urobilinogen, nitrite, microscopic (RBC, WBC))

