### Statistical analysis

#### Baseline data and Outcomes data

The effects of KRG extract or placebo treatment on the frequency, severity, and duration of symptoms related to ILI prior to the onset of influenza season will be analyzed. The Pearson chi-square test or Fisher's exact test (if the minimum expected count will be less than 2 or the ratio of expected counts lower than 5 will be more than 20%) will be used to compare the proportions of subjects reporting symptoms related to ILI and adverse events. The data will be analyzed for all of the subjects who had been randomly assigned to a group, excluding those who provided only baseline information. An intention-to-treat and per-protocol analysis will be performed.

For the subset of subjects who reported ILI-related symptoms, the total score of severity and the duration for which symptoms will be reported and the two groups will be compared using Mann Whitney U test between two groups. A value of p < 0.05 will be considered statistically significant.

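### The safety section restricts recorded adverse events to unexpected, KRG-related ones, in conflict with the all-events rule elsewhere, so the event set behind the planned between-arm comparison is undefined

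*Protocol article*

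**What the plan says.** Four places in the protocol article bear on which adverse events are collected, and a fifth uses the result.

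- **Adverse events and monitoring safety, first sentence:** "All unexpected adverse events related to KRG intake will be reported to the investigator by subjects". The investigator then writes them on the individual case report form. This is the section's only statement of what goes on that form.
- **Same section, last sentence:** vital signs are checked with "monitoring of adverse events (nausea/vomiting, fatigue, allergic reaction, and any adverse events related to KRG extract intake) after each visit". Three kinds of event are named; anything else is included if it is related to KRG.
- **Outcome measures:** "Any unfavorable or unintended sign or symptom will be documented". There is no condition on expectedness or cause.
- **Table 1 (under Secondary outcomes):** a row headed "Adverse event monitoring" is marked for Visits 3, 4, 5 and 6, also without condition.
- **Baseline data and Outcomes data:** the Pearson chi-square or Fisher's exact test is used to "compare the proportions of subjects reporting symptoms related to ILI and adverse events".

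The Randomization section sets the blinding: "Randomization sequence and allocation will be concealed to all study subjects, research staff, investigators and pharmacists until completion of the study".

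**The concern.** The collection rules differ in scope, and the analysis depends on which one is followed. The safety section puts two conditions in front of the case report form: the event must be unexpected, and it must be related to KRG. The Outcome measures section and Table 1 have neither.

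The relatedness condition is also badly suited to a blinded two-arm trial. Whoever reports or records an event does not know whether that subject took KRG, and taken literally no placebo event can meet the condition. A comparison of adverse event proportions needs events counted the same way in both arms, whatever anyone believes about their cause. Attribution belongs after recording, as a separate judgement.

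What is at stake is the completeness of the safety count. An event that is never written down cannot be restored by a later analysis plan. The Discussion also looks ahead to applying the results in children and elderly people and mentions a full-scale trial, so the safety experience of this pilot is likely to be used.

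**Working it through.** **Step 1. Compare the rules.** The plan states no figure on this point, so the main check is of the text.

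| Place | Expectedness condition | Relatedness condition |
|---|---|---|
| Safety section, first sentence | Yes, unexpected only | Yes, to KRG |
| Safety section, visit monitoring, three named events | No | Not explicit |
| Safety section, visit monitoring, other events | No | Yes, to KRG |
| Outcome measures | No | No |
| Table 1, Visits 3 to 6 | No | No |

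**Step 2. Follow three kinds of event through the rules.**

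- An unlisted event that nobody attributes to KRG is documented under Outcome measures and Table 1. Neither sentence of the safety section covers it.
- Fatigue, a named event, is picked up by visit monitoring. It is not clearly within the first sentence, because an event listed in advance is hard to call unexpected.
- An unlisted event in the placebo arm is documented under Outcome measures. Under the safety section it is kept only if someone blinded to allocation attributes it to KRG.

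The number of subjects counted with an adverse event therefore depends on the rule applied, and the statistical section does not say which count it tests.

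**Step 3. Direction of the effect.** Under blinding the conditions would be applied without knowledge of arm. Their main effect is then to remove events from both arms, which shrinks the absolute difference in recorded proportions.

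**Step 4. Illustration of lost sensitivity.** The only input from the document is 50 subjects per arm (Sample size). The 0.05 threshold is stated in the statistical section; two-sided testing is assumed. The true rates of 30% vs 10% and the capture fraction *c* are also assumptions.

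With p₁ = 0.30*c*, p₂ = 0.10*c* and p̄ = (p₁ + p₂)/2:

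- SE under the null: s₀ = √[2p̄(1 − p̄)/50]
- SE under the alternative: s₁ = √{[p₁(1 − p₁) + p₂(1 − p₂)]/50}
- Power ≈ Φ{[(p₁ − p₂) − 1.96 s₀]/s₁}

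| c | p₁ vs p₂ | s₀ | s₁ | z | Power |
|---|---|---|---|---|---|
| 1.00 | 0.30 vs 0.10 | 0.0800 | 0.0775 | 0.558 | about 71% |
| 0.75 | 0.225 vs 0.075 | 0.0714 | 0.0698 | 0.144 | about 56% |
| 0.50 | 0.15 vs 0.05 | 0.0600 | 0.0592 | −0.297 | about 38% |
| 0.25 | 0.075 vs 0.025 | 0.0436 | 0.0433 | −0.818 | about 21% |

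At *c* = 0.25 the expected count in each event cell is 50 × 0.05 = 2.5. That is below 5 in two of the four cells, so the plan's own rule would call for Fisher's exact test, and the last row is only a rough guide. With Fisher's exact test throughout, full and half capture give about 64% and 24%.

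**The case against.** The strongest reply is that the safety section never says only. It can be read as dividing the work: known effects are solicited at visits, unexpected ones are volunteered by subjects, and the Outcome measures rule and Table 1 cover the rest. On that reading the named events are not lost. Much of this stands. A reader might infer that adverse events are captured only when unexpected and related to KRG, but the document as a whole does not support that. The division of work still leaves a gap, though, because both safety-section sentences tie unlisted events to KRG and only the other two places do not.

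A reader might also infer that blinded subjects decide expectedness and relatedness, so that the test would compare guesses. The text has subjects report and the investigator record; it names no judge of either.

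A third tempting reading is that the placebo count is meaningless. The Compliance section appears to use KRG loosely for the capsules of all subjects, so in practice the condition probably works as relatedness to study product in both arms. A condition applied blind costs events and sensitivity; it does not make one arm uninterpretable. In addition, "Safety will be assessed by the reporting of clinical laboratory tests, vital sign measurements, and adverse events", and the laboratory and vital-sign data need no attribution. They do not, however, replace symptomatic events.

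Finally, a condensed article may leave definitions and causality procedures to the full protocol. That would excuse silence. It does not excuse stating two rules that disagree.

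**Conclusion.** The point holds as a conflict between stated collection rules. The safety section's wording is narrower than that of Outcome measures and Table 1, and it uses an attribution that cannot be known under blinding. It is therefore unclear which events enter the planned comparison of proportions. If the safety section is followed, events are lost in both arms and the comparison loses sensitivity.

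The size of that loss cannot be stated, because the documents give neither an adverse event rate nor a capture fraction. The fall from about 71% to about 38% power shows what half capture would cost under assumed rates of 30% vs 10%, the same capture in both arms and a two-sided 0.05 test; it is not an estimate for this trial.

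Severity is moderate. The trial is a 100-subject pilot, and adverse events are neither the primary nor a listed secondary outcome. Correction is still worthwhile, because events left off the form cannot be recovered later.

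**What to change.** Reconcile the safety section with Outcome measures and Table 1, and carry the result into the case report form:

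1. Record every adverse event in both arms, regardless of whether it is expected or thought to be related. Keep the named events as ones to be asked about, not as a limit on what is recorded.
2. Have the blinded investigator rate relatedness to study product, rather than to KRG, in a separate field after the event is recorded.
3. State in the statistical section that the comparison of adverse event proportions uses all recorded events, with related events as a subset.

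The cost is a change of wording, one form field and slightly more data entry. It should be made before data collection, since it cannot be applied in retrospect.

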#### Compliance

The KRG soft capsules remaining after each visit will be quantified in order to enhance medication compliance. Subjects whose compliance with the KRG extract capsules is ≤ 70% of the total dose will be considered to have dropped-out.

#### Sample size

This pilot study is the first clinical trials using KRG extract for Korean population. So, there was limited information about the prevention of influenza incidence or symptom releases. Therefore, we had designed a preliminary test using total 100 participants (50:50).

## Discussion

In this study, we will examine whether the KRG extract administration can significantly reduce the frequency, severity, and duration of ILI symptoms. A 1000-mg dose of KRG will be taken 3 times daily by subjects for 12 weeks. Initial ILI symptoms will be confirmed by the collaborating physician at the screening visit of self-reported ILI symptoms, and relief of symptoms will be confirmed within 7 day of the subject's self-reported recovery. Subjects will be recorded daily symptom severity in a journal using a 4-point severity score.

The aim of this study is to evaluate the efficacy of the KRG extract on the frequency, severity, and duration of ILI symptoms. For this purpose, the ability of the KRG extract to reduce the ILI incidence will be assessed in 100 healthy volunteers.

In this study, we expect that the KRG extract can effectively reduce the ILI incidence. Some studies have assessed the relative potency of ginseng extracts by evaluating their ability to prevent the upper respiratory tract infections. The ginseng extracts has been studied in 3 recent RCTs to prevent the common cold, the flu, or upper respiratory infections. Two studies did not show differences between the ginseng extract and placebo in terms of decreasing duration, severity, or frequency of overall symptoms [25,26]. One study demonstrated that the ginseng extracts decreased duration, severity, and frequency of symptoms [27].

To the best of our knowledge, there has been no report demonstrating the preventive efficacy of KRG extract on ILI incidence. Therefore, if this study will be successfully performed, the KRG extract may offer beneficial effects in reducing ILI incidence. And these results will be applied to children and elderly populations. To draw confirmative conclusion about the preventive efficacy and safety of the KRG extract on ILI incidence, a full-scale RCT is being conducted now. If there are any conclusions in the near future, we would like to publish them later.
